### Statistical analysis

2.8

Analysis will be performed on a per-protocol basis, including data only from participants who completed the full study protocol and all follow-up assessments. Statistical analyses will be conducted using SPSS version 22.0 (SPSS Inc., Chicago, IL, USA), with a significance level set at *P* < 0.05.

Demographic and clinical characteristics will be analyzed descriptively. Continuous variables will be presented as mean ± standard deviation, and categorical variables as frequencies and percentages. For between-group comparisons, continuous variables conforming to a normal distribution will be analyzed using independent samples t-tests, while non-normally distributed variables will be analyzed using rank-sum tests. Categorical variables will be compared using chi-square tests.

For the repeated measures data (including PDSS scale scores and PSG parameters) collected at baseline (Week 0), post-intervention (Week 4), and the end of the follow-up period (Week 6), the primary analysis will be performed using a linear mixed-effects model. The model will include group (REHAB vs. control), time point (as a categorical variable), and the group-by-time interaction term as fixed effects.

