### Study design

2.1

This is a single-center, prospective, randomized controlled trial designed to enroll elderly patients with advanced PD. All participants will be informed of the clinical research and the requirements for giving informed consent. The research plan and informed consent will be approved by the regional ethics committee; the trial is registered at www.chictr.org.cn (Registration number: ChiCTR2400092087).

Forty PD patients will be randomly assigned in a 1:1 ratio to the REHAB group or the control group. The control group will receive daily medication and rehabilitation therapy as recommended by the International Movement Disorders Society (31). The intervention group will receive REHAB in addition to guideline-based usual care. An independent physician will monitor the participants' health and safety via WeChat video calls.

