#### Data collection and monitoring for all participants

2.4.3

Patients in both groups must maintain a daily log tracking their blood pressure, heart rate, and body temperature. For the intervention group, these measurements will be taken immediately before and after each REHAB session. All logs, which will also note any discomfort experienced, will be submitted to the researchers via WeChat. To ensure compliance with the study protocol, a study assistant will conduct daily check-ins with all participants over WeChat video.

Our study prioritizes the tolerability and safety of REHAB for patients. Exposure to 41 °C hot water bathing is generally considered safe, even during pregnancy (27). However, PD-associated autonomic dysfunction (e.g., hyperhidrosis, anhidrosis, orthostatic hypotension) may cause discomfort. To mitigate risks, participants will be advised to drink plenty of water, wipe away sweat with a towel, and lie flat under a thin blanket for 15 min after soaking to allow blood pressure to return to normal and reduce the potential risk of syncope-related falls. If participants experience nausea, dizziness, or significant discomfort, the treatment will be discontinued.

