**PSG (Compumedics, Australia Germany, Type Grael)**			
Total sleep time (TST) (s)	X	X	
Sleep efficiency (SE) (%)	X	X	
Sleep latency (SL) (s)	X	X	
Arousal index (AI) (*n*)	X	X	
Non-rapid eye movement sleep stages N1 (%)	X	X	
Non-rapid eye movement sleep stages N2 (%)	X	X	
Non-rapid eye movement sleep stages N3 (%)	X	X	
Adverse events (AEs; *n*)		X^a^	X^b^
Adherence rate (%)		X^c^	X^d^

^a^Intervention monitoring data (V0 to Visit 1, Weeks 1–4): summarized from daily recordings. Adverse events: total count during the entire intervention period;

^b^Data from V1 to Visit 2 (Weeks 5–6);

^c^Adherence rate from V0 to V1: calculated as (number of days the participant followed the investigator's instructions/total expected days) × 100%;

^d^Adherence rate from V1 to V2: calculated similarly.

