#### Primary outcomes

2.6.1

The primary objective of this study is to assess the safety of REHAB. Adverse events will be closely monitored including: 1) symptomatic hypotension, which has been reported in association with hot bathing and may be exacerbated in PD due to autonomic dysfunction (29, 30); 2) Scald or intolerance as sensory impairments in PD may also lead to altered sensitivity to water temperature, increasing the risk of burns are intolerance to REHAB (37); 3) Systemic symptoms, such as headache, dizziness, palpitations, sweating, etc.; 4) Signs of tissue or neurovascular injury due to REHAB, including erythema, skin damage, tenderness upon palpation, and local edema.

All adverse events will be carefully assessed by trained research personnel blinded to randomization. Blood pressure, heart rate, and core body temperature we will be recorded before and after each session to further evaluate safety, and these physiological parameters will be incorporated into the safety analysis.

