### Sample size estimation

2.7

Due to the lack of prior clinical data on REHAB in this population, the study will serve as a foundational reference for future research. Prior literature (38) suggests that a sample side of 10–20 patients per group is sufficient for pilot studies. Dobkin et al. (39) note that most Phase I clinical rehabilitation pilot studies often begin with 6–12 participants. This study aims to enroll 20 patients in each group. The findings will inform safety and feasibility assessments while also guiding sample size estimations and power calculations for future Phase III trials.

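### The general tests and the total adverse-event count in the article cannot support a conclusion of safety with at most 20 participants per arm

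*Protocol article*

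**What the plan says.** Section 2.6.1 sets the aim: "The primary objective of this study is to assess the safety of REHAB". It names four groups of adverse events: symptomatic hypotension, scald or intolerance, systemic symptoms, and signs of tissue or neurovascular injury. Blood pressure, heart rate and temperature also enter the safety analysis.

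On size, section 2.7 says "This study aims to enroll 20 patients in each group". It relies on pilot-study conventions and gives no event rate, margin or power.

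Section 2.8 does not mention adverse events. Its general rules are:
- frequencies and percentages for categorical variables;
- t-tests or rank-sum tests for continuous variables;
- "Categorical variables will be compared using chi-square tests", "with a significance level set at" P < 0.05;
- a per-protocol set made up of those who finish the protocol and every follow-up assessment.

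The one analysis it calls primary is a mixed model for the sleep measures.

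In Table 1 adverse events carry the unit n, and the footnote reads "Adverse events: total count during the entire intervention period".

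**The concern.** The primary question is whether the footbath harms patients. The tools the article provides do not answer it well, for three reasons.

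- **A test is not a bound.** A two-group test with about 20 per arm will usually be non-significant even when there is a real excess of harm. What a small safety study can offer is an upper limit on the risk, and that needs an interval.
- **A total count has the wrong unit.** It adds events across sessions, so it cannot separate many patients harmed once from one patient affected repeatedly.
- **The analysis set is restricted.** Section 2.4.3 has treatment discontinued for nausea, dizziness or significant discomfort. If such participants do not count as having completed the protocol, the safety analysis loses those most likely to have had an event.

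At stake is whether the trial can give section 2.7's intended reader, the planner of a Phase III trial, a usable statement of risk.

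**Working it through.** **Inputs.** From the article: 20 per arm, 1:1 (sections 2.1 and 2.7); significance level 0.05 (section 2.8); one session a day, 5–7 days a week, for 4 weeks (section 2.4.2). Assumed: two-sided testing, the uncorrected Pearson chi-square, and the event risks below, since the article gives none. There is no power calculation to reproduce; 20 per group is simply the top of the 10–20 range that section 2.7 cites.

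**1. What no events in 20 would mean.** The exact two-sided 95% upper limit for 0/n is 1 − 0.025^(1/n).
- n = 20: 1 − 0.025^(1/20) = 16.8%.
- n = 16 (assumed, if four are lost to the completers rule): 1 − 0.025^(1/16) = 20.6%.

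Other Clopper-Pearson 95% intervals at n = 20: 1/20 gives 0.1–24.9%; 2/20 gives 1.2–31.7%; 3/20 gives 3.2–37.9%. An event with a true risk of 5% is never seen in 20 patients with probability 0.95^20 = 36%.

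**2. How often a test would detect an excess.** This sums the probabilities of all 21 × 21 possible tables for two binomial arms of 20, counting those with P < 0.05.

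| Assumed risk, REHAB vs control | Chi-square | Fisher |
|---|---|---|
| 10% vs 0% | 13% | 4% |
| 15% vs 5% | 15% | 7% |
| 20% vs 5% | 29% | 17% |
| 30% vs 10% | 36% | 24% |
| 50% vs 10% | 84% | 74% |

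A fourfold excess (20% vs 5%) would be non-significant in 100 − 29 = 71% of trials by chi-square. Among these scenarios only the last reaches 80% power.

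**3. Sparse cells.** With equal arms the expected number with an event in each arm is m/2, where m is the total with an event. It is below 5 whenever m is below 10 of 40. Single results can then turn on the approximation. For 4/20 vs 0/20:
- Pearson: 40 × (4×20 − 0×16)² / (20 × 20 × 4 × 36) = 256,000 / 57,600 = 4.44, P = 0.035.
- Fisher: 2 × C(20,4) / C(40,4) = 2 × 4,845 / 91,390, P = 0.106.

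The overall false-positive rate of the chi-square is nevertheless acceptable: 1.2%, 3.9% and 5.0% at common risks of 5%, 10% and 20%, and at most 5.3% for risks from 2.5% to 30%. Sparse cells are therefore a secondary matter.

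**4. What the total count conceals.** Each REHAB participant has 5 × 4 = 20 to 7 × 4 = 28 sessions, so the arm has 20 × 20 = 400 to 20 × 28 = 560 occasions on which an event can be logged. A total of 20 events could be one participant affected at 20 sessions (1/20 = 5%) or all 20 affected once (20/20 = 100%). The total is the same in both cases.

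**The case against.** The strongest reply is that section 2.8 never assigns a test to adverse events. The chi-square sentence is a general rule, in a paragraph that begins with baseline characteristics. If events are counted per participant, the t-test or rank-sum rule could apply instead. That is correct, and the point does not depend on which rule is used: neither gives an upper limit on risk or the number of patients harmed.

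Four stronger readings are tempting, but the article does not support them.
- **That a P value decides safety.** No passage sets such a rule or says that a non-significant result will be read as safe. The article calls the trial a basis for later research and claims no power, so low power is not in itself an error.
- **That pooled event totals will go through a chi-square test.** The Table 1 footnote describes how data are summarised, and nothing links it to that test.
- **That routine sweating will swamp the count.** Section 2.6.1 lists "headache, dizziness, palpitations, sweating, etc" as systemic symptoms, and section 2.4.3 advises participants to "wipe away sweat with a towel". That advice is a precaution. It does not say sweating is expected at every session, and events are to be assessed by blinded personnel.
- **That Fisher's test must replace chi-square.** Given the false-positive rates above, this is a trade-off: power at 20% vs 5% would fall from 29% to 17%.

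It is also fair that a fuller analysis may sit in an unseen full protocol or analysis plan, so a missing interval alone would not be a finding. What remains is what the article does state: the total-count tally, the completers-only set and the general tests. These do not suit its primary objective. Percentages and vital-sign data allow a descriptive account, but do not supply a bound.

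**Conclusion.** The point holds in limited form. For the primary safety outcome the article offers only general tests, a total event count and a completers-only set. With at most 20 per arm these cannot support a conclusion of safety: at an assumed 5% vs 20%, power is about 29% by chi-square, and 0/20 leaves risks up to 16.8% open. The bound follows from the sample size alone. The power figure rests on the assumed risks, two-sided 0.05 testing and all 20 per arm being analysed; fewer completers would make both worse. How many participants the completers rule would remove cannot be known from the article. The point concerns how safety will be summarised and interpreted. It does not show an invalid test or a faulty decision rule.

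**What to change.** In section 2.8, add a safety paragraph that:
1. analyses safety in all randomised participants by treatment received, not in completers only;
2. reports, for each adverse event category in section 2.6.1, the number and percentage of participants with at least one event by arm, with exact (Clopper-Pearson) 95% confidence intervals and a 95% confidence interval for the risk difference;
3. gives event totals descriptively only, and amends the Table 1 footnote to match;
4. treats any P value for adverse events as exploratory, and states that a non-significant difference will not be read as evidence of safety.

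No extra participants are needed, and the adverse events are already to be tracked throughout the study. Events in participants who stop bathing early must be kept in the safety data. The cost is a visibly more cautious conclusion: even with no events among 20, the trial could say only that risks above about 17% are unlikely.

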#### Secondary outcomes

2.6.2

The secondary objective of this study is to evaluate the clinical effectiveness of REHAB by examining changes in PDSS scores and objective sleep measures (TST, SE, SL, AI, N1, N2, N3) from baseline to weeks 4 and 6 post-treatment. The study will evaluate improvements and in PDSS scores and compare PSG measures between participants receiving REHAB and those in the control group. The impact of REHAB will be determined by comparing pre- and post-intervention scores within the intervention group and between the intervention and control groups.

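### The planned sleep model takes baseline as an outcome with a free group effect, so among completers it compares raw change and usually gives up precision that baseline adjustment would recover

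*Protocol article*

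**What the plan says.** Protocol article, section 2.8 (Statistical analysis), names a linear mixed-effects model for the PDSS and PSG values, which it treats as repeated measures "collected at baseline (Week 0), post-intervention (Week 4), and the end of the follow-up period (Week 6), the primary analysis will be performed using" that model. It then lists the fixed effects: "The model will include group (REHAB vs. control), time point (as a categorical variable), and the group-by-time interaction term as fixed effects". The article mentions no baseline covariate and no constraint that the arms share a baseline mean.

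Section 2.6.2 (Secondary outcomes) sets the target as "examining changes in PDSS scores and objective sleep measures (TST, SE, SL, AI, N1, N2, N3) from baseline to weeks 4 and 6 post-treatment", compared within the REHAB arm and between arms. Section 2.8 limits the analysis to a per-protocol set, "including data only from participants who completed the full study protocol and all follow-up assessments". Section 2.1 states "Forty PD patients will be randomly assigned in a 1:1 ratio to the REHAB group or the control group", and section 2.7 gives the arm size: "This study aims to enroll 20 patients in each group". Section 2.2 admits only patients with a PDSS score below 90. Table 1 schedules PDSS at baseline, Week 4 and Week 6, but PSG at baseline and Week 4 only.

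**The concern.** When Week 0 is a response and the model has a group term, each arm gets its own baseline mean. The treatment effect is then the group-by-time interaction, a comparison of raw change. Randomisation implies that the two arms have the same expected baseline, and the model makes no use of this.

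Raw change also treats each unit of baseline difference as if it carried over fully to follow-up. Where the regression of follow-up on baseline has a slope below 1, this over-corrects for chance imbalance, and such imbalance is likely in arms of 20. At stake are wider intervals for the sleep effects. Section 2.7 intends the findings to guide sample size and power for later Phase III trials, so this precision has a use.

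**Working it through.** **Inputs.** From the documents: 20 per arm (2.7), 1:1 randomisation (2.1), three fixed-effect terms and completers only (2.8), PDSS below 90 at entry (2.2). The article gives no SD, effect size, power or baseline-to-follow-up correlation. The sample size rests on a pilot convention ("10–20 patients per group is sufficient for pilot studies"), so there is no plan figure to reproduce. The correlations r below are assumptions, shown as a range.

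**Step 1: what the contrast estimates.** The mean structure is saturated in group and time and the data are complete, so the interaction coefficient at Week 4 equals

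(REHAB mean at Week 4 − REHAB mean at Week 0) − (control mean at Week 4 − control mean at Week 0).

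In five simulated complete datasets (random-intercept model, 20 per arm, three visits) the fitted interaction and the raw change difference agreed to more than 10 decimals. The same holds for PSG with two visits.

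**Step 2: chance imbalance.** The standard error of a baseline difference is √(2/20) = 0.316 SD. With slope β, follow-up is expected to differ by β times the baseline difference, but raw change removes all of it. At β = 0.5, an imbalance of one standard error moves the estimate by (1 − 0.5) × 0.316 = 0.16 SD in the opposite direction.

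**Step 3: variances with equal SDs (σ), n per arm.**
- Raw change: (2σ²/n) × 2(1 − r)
- Baseline-adjusted: (2σ²/n) × (1 − r²) × (N − 3)/(N − 4), where the last factor is the cost of estimating the slope: 37/36 = 1.028 at N = 40
- Ratio, adjusted to change: (1 + r)/2 × 37/36

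| r (assumed) | (1 + r)/2 | × 37/36 | 20 per arm performs like |
|---|---|---|---|
| 0.3 | 0.65 | 0.67 | 30 |
| 0.5 | 0.75 | 0.77 | 26 |
| 0.7 | 0.85 | 0.87 | 23 |

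In 5,000 simulated trials at r = 0.5 the variances were 0.1006 (change) and 0.0781 (adjusted), a ratio of 0.0781/0.1006 = 0.78, in line with 0.77. With an assumed true difference of 0.8 SD and two-sided 0.05, power at r = 0.5 is 0.72 with change and 0.82 with adjustment.

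**Step 4: break-even.** Setting (1 + r)/2 × 37/36 = 1 gives r = 72/37 − 1 = 0.946. With equal SDs, adjustment loses only above a correlation of about 0.95.

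**Step 5: PDSS.** The entry rule truncates baseline PDSS. For a standard normal baseline cut at c, the remaining variance is s² = 1 − cλ − λ², with λ = φ(c)/Φ(c). At c = −0.5, 0 and +0.5, λ = 1.141, 0.798 and 0.509, so s² = 0.27, 0.36 and 0.49. The cuts are assumptions, and r is here the correlation before truncation. The ratio is (1 + r)/[(1 + r) + (1 − r)s²]:
- r = 0.5: 0.92, 0.89, 0.86
- r = 0.7: 0.95, 0.94, 0.92

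Multiplying by 37/36 gives about 0.88 to 0.98, equivalent to 20/0.88 ≈ 23 down to 20/0.98 ≈ 20 per arm.

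A harsher case takes the baseline SD as 0.6 of the follow-up SD and a correlation of 0.5 or 0.7 among enrolled patients. The change-to-adjusted variance ratio is then only 1.01 to 1.02 before the slope cost. That is less than 1.028, so adjustment would lose about 1% in variance. The slopes there are 0.5/0.6 = 0.83 and 0.7/0.6 = 1.17, close to 1.

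**The case against.** The strongest reply is that nothing here is wrong. Section 2.6.2 asks for change from baseline, and the stated model estimates it without bias over randomisations. The article names no test contrast, the outcomes are secondary in a pilot without a power target, and the correlations are assumed.

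Much of this stands. A reader might infer that the planned analysis is biased or invalid; the documents do not support that, and the issue is lost precision. A reader might also infer that adjustment is free and that the gain seen with equal SDs applies to every sleep outcome. It costs about 3% in variance at N = 40, and the entry cut makes the PDSS gain small or, in the harsher case, nil.

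The unnamed contrast does not remove the point. If the Week 4 group difference were read from the same model, it would be an unadjusted follow-up comparison, with variance 1/(1 − r²) times the adjusted one before the slope cost. Neither reading uses baseline well. Nor is this detail left to a fuller document, because section 2.8 itself lists the fixed effects. Pilot status limits the weight of the point but does not remove it, given the stated use for Phase III planning.

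One further objection stands and shapes the fix. Equal expected baselines hold for everyone randomised, but not necessarily for completers. Section 2.4.3 discontinues bathing for nausea, dizziness or significant discomfort, and only one arm bathes, so completion may differ by arm. A model that forces a common baseline mean on completers could add bias.

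**Conclusion.** The point holds as one of efficiency. The stated model yields a raw-change comparison among completers, which is usually less precise than adjusting for a baseline that is already collected. With equal SDs, adjustment lowers the variance by about 33%, 23% and 13% at r = 0.3, 0.5 and 0.7. That setting is the more plausible one for PSG, which carries no entry cut of its own. For PDSS the reduction is about 2% to 12% under the truncation assumptions, and can vanish if the slope is near 1.

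All these figures assume 20 analysed per arm and correlations that the article does not give. The change is worth making because it costs little, but it does not correct an invalid analysis.

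**What to change.** In section 2.8, take only the post-baseline values as outcomes: Weeks 4 and 6 for PDSS, and Week 4 for PSG as Table 1 schedules it.
- For PDSS, fit group, time and group-by-time, with baseline PDSS and baseline-by-time as covariates.
- For each PSG measure, which has one post-baseline visit, this reduces to group plus that measure's baseline value.
- Name the adjusted group difference at each visit as the reported contrast.

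Use the alternative with a common baseline mean (Week 0 as a response, no group effect at Week 0) only if the analysis set becomes all randomised participants. Covariate adjustment does not repair selection among completers either; that belongs to the choice of analysis set.

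The cost is a wording change. No new data are needed, and the planned software fits the model. Statistically, each slope uses one degree of freedom, about 3% in variance at N = 40. That exceeds the gain only at very high correlation (about 0.95 with equal SDs) or where the slope is near 1.

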## Discussion

3

The intervention approach designed in this study is heat therapy with REHAB. Heat therapy has recently emerged as a potential alternative to physical activity and exercise, inducing physiological stressors and subsequent positive adaptation mechanisms. Extensive cohort studies and reviews have highlighted the potential of heat therapy to improve physical and mental health for patients with cardiovascular disease (40), diabetes, peripheral arterial disease (41), arterial stiffness (42), glycemic control (43), and depression (44). Moreover, heat therapy may offer additional benefits in the context of neurodegenerative diseases concerning skeletal muscle function, cerebral blood flow, and metabolic health, including Alzheimer's disease (AD) and PD (17). Heat therapy is commonly administered through various methods such as hot bathing, hot water-perfused garments (45), heat pads (46, 47), heat chambers (48), hot sand baths (49, 50), and sauna bathing (51). At home, heat therapy is typically limited to hot bathing. REHAB is designed to enhance blood circulation by achieving a comfortably warm body temperature. It is as effective as full-body bathing but less physically demanding. This method is considered a safe, simple, and easily controllable approach (29).

There are currently no established guidelines regarding the clinical parameters of minimal heat therapy for improving health markers, including heating technique, duration, intensity, and timing. However, it is feasible to develop a protocol that is tolerable, effective, and enjoyable. In this study, key parameters such as temperature, duration, and frequency are clearly defined, enhancing the intervention's practicality and applicability.

Currently, there is no standardized temperature for hot water bathing. Most fundamental studies on thermotherapy aim to elevate core body temperature (CBT) to approximately 38.5 °C−39.0 °C; however, measuring CBT in clinical practice is challenging. Previous studies have used water temperatures ranging from 40 °C to 42 °C, with 41 °C being the most frequently reported in the literature (52–54). A comparative study found that only footbaths at 41 °C significantly increased CBT, whereas lower temperatures (e.g., 40 °C) only elevated the distal-to-proximal skin temperature gradient (DPG) (55). Similarly, Horne and Reid reported that a significant increase in pre-sleep fatigue—which may aid sleep onset—occurred only following a 41 °C bath (56). In addition, our preliminary patient survey indicated that this temperature offers the best balance between comfort and acceptability.

Considering previous findings that REHAB sessions exceeding 30 min can lead to discomfort and physiological strain, often resulting in pre-mature termination of treatment (57), we propose a protocol of 30-min sessions conducted 5–7 days per week for 4 weeks (25, 27). This strategy balances efficacy with participant comfort and feasibility.

The spectrum of types of sleep disturbance in PD patients are extensive and complex. Our study utilizes the PDSS as the primary outcome measure–a validated tool for assessing sleep in PD. This instrument evaluates multiple dimensions and symptom severity through a 15-item self-administered scale. Using this scale allows for a comprehensive assessment of sleep disorders, facilitates subgroup analysis in future research, and provides deeper insights into the mechanisms linking REHAB and sleep. In addition, our study incorporates PSG as an objective assessment tool, minimizing subjective bias in sleep evaluation. This approach enables precise observation of REHAB's impact on SWS and REM sleep, thereby enhancing research accuracy and robustness.

Importantly, hot bathing has long been utilized in medical practice as a therapeutic intervention (58). It offers the advantage of being easily implemented at home without requiring specialized equipment or professional supervision. Additionally, we provide clear guidelines regarding techniques, temperature, duration, and frequency to enhance both adherence and generalizability. This study contributes valuable insights into strategies for improving the quality of life for patients with advanced PD.

A primary limitation of this study stems from its open-label design. Firstly, due to the nature of the intervention (lower extremity hot water bathing), blinding of participants and treatment providers is not feasible, inevitably introducing the risk of performance bias. For instance, participants in the REHAB group, aware of receiving a novel intervention, may experience a stronger placebo effect due to positive outcome expectations or may more actively adhere to other sleep hygiene recommendations. Similarly, researchers may unintentionally devote more attention when guiding the REHAB group. Secondly, although we employed an outcome assessor-blinded design—where the neurologists responsible for collecting and analyzing polysomnography (PSG) data and assessing adverse events remain completely unaware of group allocation—the self-reported Parkinson's Disease Sleep Scale (PDSS), a subjective outcome, cannot avoid reporting bias introduced by the participants' own unblinded status. This constitutes one aspect of detection bias. By including objective PSG parameters as a core secondary endpoint, we aim to provide evidence for improvements in sleep architecture that is less influenced by subjective expectations, thereby partially mitigating this limitation. In future Phase III confirmatory trials, if feasible, consideration could be given to designing a “sham bathing” control (e.g., using water near skin temperature) to achieve participant blinding and more rigorously control for these biases.

Future research can build upon these findings by incorporating multicenter, large-sample designs. Such studies should examine the applicability of REHAB across various age groups, disease stages, and comorbidities, further expanding its clinical relevance and impact.

This study is designed to evaluate the safety and efficacy of REHAB as a rehabilitation intervention specifically for elderly patients with advanced PD who suffer from sleep disorders. The primary objective is to assess whether this therapy can be safely administered and whether it improves sleep quality in these patients. The experimental outcomes will help establish a novel rehabilitation strategy that could be integrated into guideline-based usual care for PD patients with sleep issues, especially for elderly patients with mobility limitations or other comorbidities. The results of this study will be instrumental in guiding future research and clinical practices.
